## Discussion

The expected outcome of this study is that the mindfulness-based cognitive programme will lead to improvements in resilience and reduction of smartphone addiction risk among adolescents. The MBCP enables the adolescents to grasp a new skill to manage their emotion by attending to the present and modify their cognitive thoughts toward stress and difficulties encountered in life. Throughout the training process, the adolescents will learn that they can manage their emotion through daily mindfulness practice. The programme has a lifelong benefit to adolescents as it enables them to manage their stress and conflicting thoughts which linger in adolescents with a simple and economical approach.

Problematic smartphone use, when not managed timely and adequately, may progress to smartphone addiction and other associated negative health outcomes. Our intervention can be served as a preventive intervention to be applied regularly in schools and other adolescent health centers to strengthen adolescents’ resilience in order to boost up their resistance against addictive smartphone use. Nurses, being one of the major frontline healthcare providers in the community to monitor people’s health and provide health promoting intervention, could integrate this noninvasive and simple-to-administer intervention into existing adolescent wellness programmes to not merely manage smartphone use issue but also to promote the overall wellbeing of the adolescent clients.

It is hoped that findings from the study could lead to larger, multisite trials to provide more robust evidence. In addition, similar evidence-based approaches can be developed in the future for other age groups who are vulnerable to smartphone addiction to strengthen the protection against the negative effects of smartphone use.

There are several limitations of this protocol. This study targets early adolescents; the generalizability of the study findings to middle- and late-adolescents is unknown. As two treatment groups will receive treatments in totally different formats, ascertainment bias might be introduced to the results although the study hypotheses will not be made known to the schools, the parents and the students. Only four primary schools will be recruited; the similarity in characteristics exhibited by participants from the same school may bias the results. To assess the impact of potential clustering of the participants from the same school, Generalized Estimating Equation model will be adopted to control the cluster effect of school.

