### Study design and setting

This study will be an open-label, parallel-group, cluster randomized controlled trial with repeated measurement analysis. It will pragmatically evaluate the effects of the mindfulness-based cognitive programme (MBCP) on improving adolescents’ resilience, changing their smartphone behavior and reducing smartphone addictive symptoms as compared with the control group at five measurement points (i.e. baseline (T0), one month (T1), two months (T2), three months (T3) after the programme, three months’ follow up (T4)). The study will be conducted in four primary schools in Hong Kong. The primary schools will be the unit of allocation, and individual participants will be the units of analysis. The intervention group will receive the mindfulness-based programme, and the control group will receive existing counselling services for students with emotional/behavioral problems. (i.e. treatment as usual). Data collection will be started in September 2020. Key aspects of the study design can be found in Fig. 1. We designed and reported this study protocol according to the SPIRIT2013 statement.

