### Sample size calculation

As it is the first study investigating the effect of the MBCP on smartphone behavior in adolescents, the project team can only decide the predicted intracluster correlation with reference to other studies investigating adolescent behavioral problems. The predicted intracluster correlation of 0.01 is adopted based on studies about smoking prevention and alcohol use in adolescents [55, 56]. 20 % potential dropout/noncompliance rate is considered reasonable. Assuming a Type 1 error of 0.05 and Type II error of 0.2, a total of 240 participants (i.e. 120 in each group, 60 in each school) is required to achieve a medium effect (Cohen’s *d*) of 0.5 [57] for comparing the treatment effect between the two treatment groups and among the measurement points within groups for the three outcomes to be measured – resilience, smartphone behavior and symptoms of smartphone addiction.

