### Randomization and blinding

The four participating schools will be cluster-randomized at a ratio of 1:1 into the intervention and control groups by coin toss by the research assistant A (RA-A) who will not be involved in participant recruitment and data collection. All students recruited under the same participating school were exposed to the same intervention. The principal investigator, who will be responsible for recruiting the schools and the students, will code the participating schools with a number and a letter to represent the district and the school, respectively. RA-A will only know the four codes but not the names of the schools. The school will be assigned to the intervention group if the landed side is heads; the school will be assigned to the control group if the landed side is tails. The allocation result will be kept by the RA-A in a sealed opaque envelope until participant recruitment. The school teachers, parents and students will not be informed of the research hypotheses. RA-A will feed data into the computer in separate datasheets so that the co-investigator responsible for data analysis can analyze data without having access to information about the allocation. Hence, it is a single-blind design.

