### Data analysis

IBM SPSS version 23 will be used for statistical analysis. Mean and standard deviation will be reported for continuous variables, i.e. age, types of smartphone functions used and total resilience score. Frequency and percentage will be reported for nominal and ordinal variables. Cronbach’s alpha and intra-class correlation coefficients will be calculated to determine the validities and reliabilities of the two scales: the translated Smartphone Addiction Scale and the Chinese Version of Conner-Davidson Resilience Scale – 25. Independent t-test/Mann-Whitney U test will be used to compare the socio-demographic variables between intervention and control groups. Generalized Estimating Equation model will be used to verify all the hypotheses. The socio-demographic variables will be treated as co-variates to adjust the group means. Results will be reported with 95 % confidence interval. Intention-to-treat analyses will be applied to the independent and dependent variables. Missing data will be handled by replacing the missing values with the item-specific mean. Tests performed will be two-tailed with alpha value set at 0.05. Cohen’s *d*, calculated by taking the difference of the adjusted means between two comparison groups and dividing it by the pooled standard deviation, will be used to estimate the effect size of the treatment.

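### With two schools per arm, GEE cannot deliver the control of school clustering that the protocol claims for it

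*Protocol article*

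**What the plan says.** Under Randomization and blinding, "The four participating schools will be cluster-randomized at a ratio of 1:1 into the intervention and control groups", so each arm holds two schools. Under Study design and setting, "The primary schools will be the unit of allocation, and individual participants will be the units of analysis".

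The Data analysis section states that "Generalized Estimating Equation model will be used to verify all the hypotheses", with two-tailed tests at 0.05 and 95% confidence intervals. The primary objective concerns group-by-time interaction effects, and there are five measurement points, T0 to T4.

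The limitations paragraph of the Discussion concedes that "Only four primary schools will be recruited" and that similarity among pupils of one school may bias the results. Its answer is that a "Generalized Estimating Equation model will be adopted to control the cluster effect of school".

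The article names neither the GEE cluster variable, nor the variance estimator, nor a small-sample correction, nor the reference distribution.

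**The concern.** GEE inference is justified by a large number of independent clusters. For the effect of a programme allocated by school, the independent units are the four schools, which leave 4 − 2 = 2 degrees of freedom between schools within arms. More pupils per school do not add to that number.

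All three primary hypotheses and their confidence intervals rest on this model. If its standard errors are too small or too unstable, the trial can report a programme effect on resilience, smartphone use or addiction symptoms when two schools merely differ from two others. The limitations paragraph tells the reader that the chosen method has dealt with this risk.

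**Working it through.** **Inputs.** Four schools, two per arm; "120 in each group, 60 in each school"; "The predicted intracluster correlation of 0.01 is adopted"; "Assuming a Type 1 error of 0.05 and Type II error of 0.2"; d = 0.5; 20% dropout, so 60 × 0.8 = 48 analysed per school.

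**The plan's own figure.** Without clustering, d = 0.5 needs 63 per arm. The design effect is 1 + 59 × 0.01 = 1.59. Then 63 × 1.59 × 1.2 = 120.2 per arm, which reproduces 240 in total. The calculation allows for the ICC but not for having only 2 between-school degrees of freedom.

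**School as the GEE cluster.** Let d₁ and d₂ be the differences between the two school means within each arm, and D the difference between arms. Schools are of equal size.
- The uncorrected sandwich variance of D is (d₁² + d₂²)/8. Each squared difference has expectation 2σ², where σ² is the variance of a school mean, so the sandwich has expectation σ²/2. The true variance of D is σ².
- The ordinary two-sample t statistic uses (d₁² + d₂²)/4 and has 2 df. The robust Wald statistic is therefore z = √2 × t₂.
- Type I error = P(|t₂| > 1.96/√2) = P(|t₂| > 1.386). For 2 df, P(|t| > x) = 1 − x/√(2 + x²), so the error is 1 − 1.386/1.980 = **0.300**. Neither the ICC nor the school size enters.
- Simulation agrees: 0.300 on school means, 0.301 for a fitted exchangeable GEE with robust standard errors, 0.292 with model-based ones, and 0.29–0.31 for a T3-versus-T0 group-by-time contrast.
- With time as a five-level factor, an omnibus interaction test has 4 df. Each arm's two school residuals sum to zero, so each arm contributes rank 1. The robust covariance of the four terms had rank 2 in every simulated data set checked, so it cannot be inverted.

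**Partial corrections with school as the cluster.**
- Unbiased variance, normal reference: P(|t₂| > 1.96) = 0.189.
- Uncorrected variance, t₂ reference: P(|t₂| > 4.30/√2) = 0.093.
- Both corrections together: 0.05.

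**Student as the GEE cluster.** School is ignored.
- Arms compared at one visit: the design effect is 1 + 47 × 0.01 = 1.47 and the error is 2[1 − Φ(1.96/√1.47)] = **0.106**. At an assumed ICC of 0.05 the design effect is 3.35 and the error 0.284.
- Group-by-time contrast (T3 − T0): a school effect that is constant over visits cancels. Simulated with an assumed within-student correlation of 0.5, the error is about 5% at stable ICCs of both 0.01 and 0.05.
- If half of the 0.01 varies by visit (assumed), the school variance of the change is 2 × 0.005 = 0.01, against 2 × 0.99 × 0.5 = 0.99 within school. The ICC of the change is 0.01 and the error 10.6% (simulated about 11%).
- If all of it varies (assumed), the ICC of the change is 0.02/1.01 = 0.0198, the design effect 1.93 and the error 15.8% (simulated about 16%).

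**Power of a valid test on 2 df** (critical value 4.30, d = 0.5, ICC 0.01, one-visit comparison without baseline adjustment).
- 48 per school: noncentrality 0.5/√(2 × 1.47/96) = 2.86; power 36%.
- 60 per school: noncentrality 0.5/√(2 × 1.59/120) = 3.07; power 40%.

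**Permutation.** Four schools split 2:2 give six allocations, so the smallest two-sided p is 2/6 = 0.33.

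**The case against.** The strongest reply is that the article fixes neither the cluster variable nor the variance estimator, and that such details are commonly left to an analysis plan, which is not shown. This stands as far as the 30% is concerned: that figure is conditional, and the article does not commit the trial to it. It does not rescue the claim. The article asserts that GEE deals with school clustering, and under either choice of cluster an uncorrected GEE does not. An unseen plan could restore the 5% level only with both a corrected variance and about 2 df, and the stated 80% power would then be wrong.

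Three stronger readings are tempting but unsupported.
- *That the planned interaction test cannot be computed.* The article commits to no 4-df joint test and does not declare time a factor. Single contrasts and a linear-time interaction can be computed, and with the student as cluster so can the joint test.
- *That with the student as cluster the primary test must be badly inflated.* The 10.6% and 28% belong to a comparison of arms at one visit. School differences that are stable over time cancel from a change contrast.
- *That a significant result would probably be school variation.* A type I error rate is not the probability that a given positive finding is false.

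The authors also disclose the four-school limit and hope for larger trials. That is to their credit, but they offer GEE as the answer to it.

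**Conclusion.** The concern holds in conditional form. With two schools per arm, GEE as described does not control school clustering.
- **School as cluster, uncorrected:** about 30% type I error at nominal 5% for an arm contrast or a single group-by-time contrast. This is exact for equal school sizes and normally distributed school means, and free of the ICC. An omnibus 4-df test, if one were intended, would be singular.
- **Student as cluster:** 10.6% for a one-visit comparison at the plan's ICC. For a group-by-time contrast the error runs from about 5% to 16%, depending on how much of the ICC varies by visit, which the article does not give.

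A significant programme effect could therefore not be reliably separated from differences between schools. The cause is the four-school design. Changing the test restores the error rate but not the power.

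**What to change.** 1. For the arm contrasts, replace the uncorrected GEE Wald test with either a comparison of baseline- and covariate-adjusted school means, two against two, or a linear mixed model with random school and student effects. Take tests and confidence intervals from t on 2 df (multiplier 4.30).
2. Pre-specify one contrast per outcome, for example the change to T3.
3. Do not make a permutation test the decision test, since it cannot reach 0.05.
4. In the limitations paragraph, withdraw the statement that GEE deals with the school effect, and say that two schools per arm limit what can be attributed to the programme.
5. In the sample size section, restate the power at d = 0.5 and ICC 0.01 as about 36% (48 per school) to 40% (60 per school).

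The secondary hypothesis on student-level associations is not an arm contrast and does not need the 2-df reference.

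The cost is a change of text and no new data, but the intervals widen (multiplier 4.30 instead of 1.96) and the stated power falls to about half of that planned. Recovering it would take more schools; more pupils in the same four help little, as the step from 48 to 60 per school shows.

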## Data Availability

Not applicable.

## Abbreviations

MBCT: Mindfulness-based cognitive therapy.
MBCT-C: Mindfulness-based cognitive therapy for children.
MBCP: Mindfulness-based cognitive programme.
RA-A: the first research assistant.
RA-B: the second research assistant.
CD-RISC-25: Connor-Davidson Resilience Scale − 25.
SAS-SV: Smartphone Addiction Scale–Short Version.
